### 2.7. Study Outcomes

#### 2.7.1. Primary Outcome

The primary outcome measure for the study will be the count of negative opioid UDS (excluding BUP) over 16 weeks. Scheduled appointments for a UDS that are missed will be conservatively imputed as positive for opioids.

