#### 2.7.2. Secondary Outcome

Retention as defined as completion of the 16-week outpatient treatment without interruption. All participants who miss three consecutive appointments will be judged to have discontinued treatment.

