#### 2.7.3. Exploratory Outcomes

There is change in psychosocial functioning from baseline at the end of the 16-week treatment. There is correlation of participant demographics, clinical data, BUP EL.R, and BUP/NX-F maintenance dose with the primary and second outcome.

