### 2.8. Sample Size Calculation

Given the novelty of the study, the sample size was estimated indirectly with reference to the relevant CM literature as reviewed by the UK National Institute of Care Excellence (NICE Clinical Guideline 51; Appendix 15 [56]. The study was powered for 80% to detect a difference of 3 weeks opioid abstinence as evaluated by NICE for three trials (an odds ratio in favour of CM of 2.56; 95% CI 1.76 to 3.72). Using this pooled effect, uplifted by 15% for attrition and with a 5% two-sided alpha, it was estimated that 92 participants should be allocated to the experimental and control group.

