### 2.9. Statistical Analysis of the Primary and Secondary Outcomes

Data for the whole population and by study group will be analysed for mean, standard deviation, 95% confidence interval, and range. With no interim analysis, all statistical analyses will be pragmatically done according to intention-to-treat principle. All analyses will be conducted using two-sided 5% significance test. A fixed-effects logistic model will be applied to analyse the primary outcome. To analyse between group differences, student* t*-test will be conducted for normally distributed data, or a Mann-Whitney test. For the primary outcome, a planned sensitivity analysis will determine the impact of the imputed or complete case [57]. Alternatively, reported observed opioid screens or actual screens without imputation will be analysed between group differences. Secondary outcome will be evaluated using proportional hazards regression model and Chi-Square test will be performed to measure between group differences.

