### 2.10. Analyses for Exploratory Outcome

Bivariate correlation tests to explore correlations with study outcomes will be performed. Specifically, Pearson's correlation will be applied for continuous and Spearman's rho test for categorical data. Factors demonstrating significant correlation and those with potential impact on the primary outcome will be studied for predictive power using a simple linear regression model. Finally, analysing for the effect of confounders will be done using univariate analyses for factors generating higher correlation (>0.5). The mean change from baseline scales or within group change will be analysed using a generalised linear model framework. A paired* t*-test will be conducted where normal distribution is assumed or alternatively Kruskal-Wallis test. The magnitude of change from baseline will be estimated using bias corrected Hedge's* g* effect size. Mean difference between groups will be analysed using student* t*-test where normal distribution is assumed or a Mann-Whitney test.

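### The tests named for change in psychosocial functioning use only participants with a week-16 score, so they may become complete-case analyses that do not match the intention-to-treat statement; a repeated-measures model on the Table 2 assessments would avoid this

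*Protocol article*

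**What the plan says.** **Outcome.** Protocol article, section 2.7.3, sets a single end point in time: "There is change in psychosocial functioning from baseline at the end of the 16-week treatment".

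**Analysis.** Section 2.10 says: "The mean change from baseline scales or within group change will be analysed using a generalised linear model framework". It gives no time points and no repeated-measures structure. It then names a paired t-test, which "will be conducted where normal distribution is assumed or alternatively Kruskal-Wallis test", a bias-corrected Hedges' g for the size of the change, and a comparison of the arms: "Mean difference between groups will be analysed using student" t-test, or Mann-Whitney.

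**Population.** Section 2.9, on the primary and secondary outcomes, states that "all statistical analyses will be pragmatically done according to intention-to-treat principle".

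**Discontinuation and missing data.** Section 2.7.2: "All participants who miss three consecutive appointments will be judged to have discontinued treatment". Section 2.7.1: "Scheduled appointments for a UDS that are missed will be conservatively imputed as positive for opioids". Section 2.9 adds a sensitivity analysis of that imputation, for the primary outcome only. The sample size in section 2.8 was "uplifted by 15% for attrition and with a 5% two-sided alpha".

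**Assessments.** Table 2 schedules every psychosocial scale at baseline, in weeks 1 to 4 and at week 16. PHQ-9 and GAD-7 are also given in weeks 9 to 12, and PSQI in every four-week block.

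**The concern.** A paired t-test, a Hedges' g on change and a two-group test on change all need a week-16 score for each participant they include. Anyone without one is left out. These tests cover the whole randomised population only if everyone is assessed at week 16, and the article does not describe how participants who stop treatment would be followed.

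The article's own Introduction suggests that such loss would not be random. It links depression and anxiety to discontinuation, impulsiveness to noncompletion and sleep disorders to poorer engagement. PHQ-9, GAD-7, BIS-11 and PSQI measure these same traits.

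Loss may also differ by arm. Retention is itself the outcome compared between arms. The Introduction says that supervised dosing may lead to dropout, and Table 3 gives supervised outpatient dosing to the experimental arm only.

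At stake are the within-group change, its effect size and, if loss differs by arm, the comparison between arms.

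**Working it through.** **1. What each analysis needs.**

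| Item | Week-16 score needed? | Interim scores used? |
|---|---|---|
| Paired t-test | Yes | No |
| Hedges' g for change | Yes, if computed from paired scores | No |
| Two-group test on change | Yes | No |
| Generalised linear model framework | Not stated | Not stated |

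**2. How many may be lost.** The article gives no rate of missing week-16 questionnaires. I use the 15% attrition allowance in section 2.8 as a stand-in. Reading 92 as the number per arm (the wording is ambiguous), 92 × 0.85 = 78.2, so about 14 per arm would lack a pair. If 92 is the total, 46 × 0.85 = 39.1 pairs per arm.

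**3. Size of the bias in general.** With a proportion d lost,

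bias in mean change = d × (mean change in completers − mean change in those lost).

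For assumed gaps of 0.25, 0.5 and 1.0 SD:
- d = 0.15: 0.04, 0.08 and 0.15 SD
- d = 0.30: 0.08, 0.15 and 0.30 SD

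Between arms with the same gap, the bias is the difference in loss times the gap. It is 0 with equal loss. With 10% against 20% loss it is 0.10 × gap = 0.025, 0.05 and 0.10 SD.

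**4. Direction.** The article gives no SD, correlation or expected change, so these inputs are assumptions:
- true change -0.50 SD;
- correlation with the week-16 score of 0.3 for baseline, 0.6 for weeks 1 to 4 and 0.75 for weeks 9 to 12;
- logistic dropout, with the odds multiplied by 1.6 to 2.7 per SD worse score.

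Simulated mean change among completers:

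| Loss | Latest interim score drives dropout | Baseline score drives dropout |
|---|---|---|
| 15% | -0.52 to -0.55 | -0.45 to -0.41 |
| 25% | -0.54 to -0.58 | -0.42 to -0.35 |
| 40% | -0.57 to -0.62 | -0.37 to -0.27 |

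The two mechanisms push in opposite directions. Losing people with poor interim scores removes poor outcomes and flatters the change. Losing people who were severe at baseline removes those with most room to regress towards the mean, and understates it. Varying the baseline-to-interim correlations from 0.3 to 0.5 moves the first entry at 15% loss only to -0.51 to -0.56.

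**5. Against sampling error.** The standard error of a paired mean change in SD units is √(2(1 − 0.3)/n).
- 15% loss, n = 78: √(1.4/78) = 0.134. Shifts of up to 0.05 and 0.09 are 0.37 and 0.67 standard errors.
- 40% loss, n = 92 × 0.60 = 55.2: √(1.4/55.2) = 0.159. Shifts of up to 0.12 and 0.23 are about 0.75 and 1.4 standard errors.

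**6. Does the remedy work?** A likelihood analysis using baseline and interim scores returned -0.50 in every scenario in which dropout depends on observed scores, whichever way the completers' bias ran. That condition is built into the scenarios, so this shows what the model can do and does not prove that it will hold in this trial.

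**The case against.** The strongest reply is that the article is condensed, the outcome is exploratory, and missing-data handling for exploratory scales is usually left to the full protocol or analysis plan, which is not shown. That stands as far as it goes: the absence of a missing-data rule is no finding in itself. The point rests on what is stated, namely one end time point with tests that need a score at it, beside an intention-to-treat claim for all analyses.

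A reader might infer four stronger things, which the documents do not support.

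- *That discontinued participants cannot reach week 16.* Section 2.7.2 defines stopping treatment, not leaving the study. Table 3 lists end-of-study assessments for both arms without a condition on retention. The fair wording is that they may lack a score.
- *That the interim scores will go unused.* The paired and two-group tests do not use them, but the generalised linear model framework is silent on time points and could.
- *That improvement is overstated.* The sign depends on the dropout mechanism. The Introduction treats depression and anxiety as patient characteristics, which points more directly to baseline severity and so to understatement.
- *That section 2.9 is flatly contradicted.* The intention-to-treat sentence sits in the section on primary and secondary outcomes and can be read as analysis by allocated arm. The mismatch arises only if week-16 scores are missing.

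It is also fair that the 15% is a sample-size allowance for the abstinence outcome, and that all sizes in SD units are assumed.

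**Conclusion.** The point holds in a limited form. If participants who discontinue lack a week-16 score, the paired t-test, Hedges' g and two-group test on change become complete-case analyses that do not match the declared intention-to-treat principle. The article's own account of who drops out makes bias plausible but does not fix its direction.

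Under the simulated assumptions the shift at 15% loss is 0.02 to 0.09 SD either way, under one standard error. It would pass one standard error (0.15 against 0.134) if completers and those lost differed by a full SD in mean change. It grows with more loss, and it reaches the comparison between arms if loss differs by arm. None of these sizes can be computed from the article alone. The point is minor, because the outcome is exploratory, but the remedy needs no new data.

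**What to change.** In section 2.10:

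1. State whether participants who discontinue treatment are still assessed at week 16.
2. Specify the generalised linear model framework as a mixed model for repeated measures on all randomised participants, using the outpatient assessments in Table 2, with arm, visit and arm-by-visit terms.
3. Enter baseline either as a response or as a covariate, not both. Where it is a covariate, keep all randomised participants with a baseline score in the reference population, and evaluate the week-16 estimate at their mean baseline.
4. Report the week-16 change, the difference between arms and Hedges' g from that model.
5. Label any paired or two-group test that is kept as complete-case.

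The cost is analysis wording and a slightly more complex model. The model assumes that dropout depends on observed scores. The gain is smaller for WSAS, BIS-11 and ASI-Lite, which have only one interim assessment (weeks 1 to 4), so later deterioration before dropout would not be seen.

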**Methods:**

The Suboxone Treatment and Recovery Trial (STAR-T) is a single site, 16-week, parallel-group, randomised controlled trial. The aim of the study is to determine the effectiveness of a medication management framework including TDM and UDS to enable patients enrolled on outpatient OAT (with buprenorphine/naloxone [sublingual film formulation; BUP/NX-F; Suboxone™]) to receive stepped take-home doses. Following stabilisation during inpatient care, adult participants with illicit or prescription OUD were allocated (1:1) to receive (1) BUP/NX-F plus medication management for take-home doses based on TDM, UDS, and contingency management protocol (the experimental group) or (2) BUP/NX-F plus UDS only (treatment-as-usual, the control group). The primary outcome is the mean percentage of negative UDS over 16 weeks. The secondary outcome is treatment retention defined as completion of 16 weeks of OAT without interruption. There will be an exploratory analysis of the association between participant characteristics, clinical data, and outcomes.

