Several patient characteristics are associated with sub-optimal OAT response. Younger patients [14] and those with unstable housing [15] tend to have a higher risk of treatment discontinuation. Co-occurring mental health disorders have a prevalence of 40 to 55% in this clinical population [16] and may be associated with compromised treatment response [17]. In particular, depression and anxiety disorders are often reported to predict treatment discontinuation [18] and heroin use [18]. Personality disorders (particularly borderline personality disorder) are associated with poor prognosis of substance use treatment [19]). An impulsive personality trait has been observed to predict noncompletion of SUD treatment [20]. Sleep disorders are associated with day-time dysfunction in the heroin using population which may compromise patient engagement in treatment [21].

Buprenorphine and naloxone (BUP/NX; ratio 4:1; and a sublingual film formulation [Suboxone®; BUP/NX-F developed for rapid dissolution]) have been developed for maintenance OAT with the aim of suppressing the likelihood of illicit opioid injecting (because the opioid antagonist naloxone may cause opioid withdrawal) and maximising adherence (because BUP/NX-F is very hard to remove once placed under the tongue). In contrast to BUP mono therapy, there is evidence that these alternative formulations deliver further reduction in diversion [22]. A ‘pill or medication count' practice has also been recommended as part of the effort to increase medication adherence [23] but, to date, there are no reported randomised controlled trials.

Therapeutic Drug Monitoring (TDM) is a patient centered and precision medicine tool that involves quantitation and interpretation of medication blood concentrations with necessary dose adjustments to optimise treatment outcomes [24]. It has been applied in neuropsychiatry to enhance outcomes of antiepileptics [25], antipsychotics [26], and mood stabilisers [27] and for monitoring drug-drug interactions [28]. The potential value of TDM in OAT has been recognised as a monitor of compliance [24] yet there is no consensus or guidelines on how it should be clinically implemented and there have been no published clinical trials.

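### The exploratory search for factors associated with opioid use relies on an outcome that falls with dropout, so a factor that predicts only dropout can appear as a predictor of use

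*Protocol article*

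**What the plan says.** - **Aims (section 2.2).** The two exploratory aims look for associations of demographics, buprenorphine elimination rate and dose, and psychosocial functioning with two things: opioid use and treatment retention.
- **Exploratory outcome (2.7.3).** "There is correlation of participant demographics, clinical data, BUP EL.R, and BUP/NX-F maintenance dose with the primary and second outcome".
- **Primary outcome (2.7.1).** "The primary outcome measure for the study will be the count of negative opioid UDS (excluding BUP) over 16 weeks", and "Scheduled appointments for a UDS that are missed will be conservatively imputed as positive for opioids". The abstract words it as a percentage: "The primary outcome is the mean percentage of negative UDS over 16 weeks".
- **Discontinuation (2.7.2).** "All participants who miss three consecutive appointments will be judged to have discontinued treatment".
- **Exploratory method (2.10).** "Bivariate correlation tests to explore correlations with study outcomes will be performed". Factors with a significant correlation go on to a linear regression for predictive power.
- **Analysis without imputation (2.9).** "reported observed opioid screens or actual screens without imputation will be analysed between group differences". Section 2.10 has no counterpart.
- **Candidate factors (Introduction).** "depression and anxiety disorders are often reported to predict treatment discontinuation"; the same sentence goes on to name heroin use as well. Younger age is linked to discontinuation and impulsivity to non-completion.

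**The concern.** The aims name two targets, but the variable used for the first already contains the second. A participant who stops attending accrues no more negatives, and any further scheduled screens are scored positive. A factor with no relation to drug use, but with a relation to leaving, is then correlated with the variable that represents opioid use.

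Scoring missed screens as positive is described as conservative. In a predictor search it is not, because it can create associations. Such a factor could be reported twice, once for retention and once for opioid use, and the second report would have no support in the urine results. Because section 2.10 carries significant correlations into regression, the error can propagate.

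**Working it through.** The plan gives no figure on this point, so there is none to reproduce. The check has three parts.

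**1. One participant.** Assume 16 weekly screens, a 0.70 chance that each is negative, and departure after 8 screens. Expected negatives are 8 × 0.70 = 5.6.
- Count: 5.6, against 16 × 0.70 = 11.2 for a completer with the same use.
- Percentage, missed screens imputed to week 16: 5.6/16 = 35%.
- Percentage, imputed only up to the third missed screen: 5.6/11 = 51%.
- Percentage of attended screens: 5.6/8 = 70%.

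Dropping the imputation but keeping a raw count changes nothing, since a missed screen adds no negative either way.

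**2. How often this gives a significant result.**

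From the documents: two-sided 5% level (2.9), 16 weeks, 15% attrition allowance (2.8), three missed appointments as discontinuation (2.7.2). Section 2.8 can be read as 92 per group or 92 in all, so n = 184 and n = 92 are both shown.

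Assumed, because the article does not give them:
- weekly screens;
- factor X ~ N(0,1), unrelated to use;
- exponential dropout time with hazard ratio (HR) 1.5 or 2.0 per SD of X;
- each participant's chance of a negative screen ~ Beta(2.1, 0.9), with mean 2.1/3.0 = 0.70.

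With *a* screens attended and *k* negative, a Pearson test was applied to (a) k/16, (b) k/min(16, a+3) and (c) k/a. Because X is unrelated to use, E[k | X] = 0.70 × E[a | X]. Outcome (a) therefore follows X through attendance alone, while E[k/a] = 0.70 whatever *a* is.

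Share of simulated trials with p < 0.05. Paired values are HR 1.5 / HR 2.0, and ranges span repeat runs of at least 2,000 trials:

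| n, dropout | (a) count, or imputed to week 16 | (b) three misses imputed | (c) attended only |
|---|---|---|---|
| 184, 15% | 18–19% / 41–42% | 12–13% / 23–27% | 4–6% |
| 92, 15% | 11–12% / 23–24% | 8–9% / 14–16% | 4–6% |
| 184, 30% | 45–46% / 87–88% | 28–29% / 63–66% | 5–6% |

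With HR 1.0 every column is about 5%, so the excess comes from dropout. Counting the screen in the week of leaving as attended lowers the first row to 16% / 36% and 10% / 20%.

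**3. A different model.** This used a binary factor split 50/50, uniform dropout times and a 20% positive rate. With dropout of 10% against 20% (average 15%), the count is significant in about 11% of trials at n = 92 and 15–16% at n = 184. With 20% against 40%, it is 22–23% and 42%. Attended screens stay near 5%.

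**The case against.** **The plan uses its own measure.** Section 2.7.1 defines how the trial measures opioid use, and correlating factors with that measure is consistent. Retention is correlated separately, so a careful reader could see the overlap. This is fair, and it limits the weight of the point. Nothing in section 2.10 requires the comparison, however, and the analysis without imputation stops at group differences. That an analysis plan might add detail does not change what the article fixes as the variable.

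**Leaving may itself reflect relapse.** The simulation assumes that dropout is unrelated to use. If participants return to use and then stop attending, the factor is a true predictor of use. With that reading in the same set-up (n = 184, 15% events), the imputed count detects the factor in 17–39% of trials and attended screens in 4–5%, which is chance. With one positive screen given before leaving, attended screens reach about 8–14%. This objection stands. A reader might infer that attended screens should decide, so that a factor absent there is only a retention factor. The data do not support that rule.

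**Depression and anxiety.** A reader might infer that these would correlate with the outcome through dropout alone. The Introduction does not support this, since it says they are also reported to predict heroin use.

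**Conclusion.** The point holds as a minor one. As defined, the variable that represents opioid use in the exploratory search falls with dropout, so a factor that predicts only dropout can appear as a predictor of use.

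At the plan's 15% attrition and under the stated assumptions, this happens in about 18–42% of trials at n = 184 and 12–23% at n = 92 on the count. If only three misses are imputed it is about 12–26% and 8–15%. The nominal rate is 5%. A reader might infer that such a factor will be reported as a predictor of use. The figures do not support that certainty: at 15% dropout it occurs in fewer than half of trials.

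The size depends on the screening schedule, the share of negative screens and the strength of the link to dropout, none of which the article gives. It also depends on two matters the article leaves open: count or percentage, and whether appointments after discontinuation still count as scheduled. These change the size of the effect, not its presence. The treatment comparison, the sample size and the decision rules are not affected.

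**What to change.** In section 2.10, run each correlation and regression for opioid use twice: on the imputed primary outcome, and on the percentage negative among attended screens. Present both beside the association with retention.

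Where an association appears only on the imputed outcome and on retention, state that the data cannot distinguish opioid use from dropout for that factor. Do not label it a predictor of use, and do not label it purely a retention factor.

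The cost is one extra column of exploratory results from data already collected. Section 4 says that analysis is still in progress, so the column can be added and marked as an addition. The drawback is that attended screens carry their own selection if participants leave because of relapse, which is why both versions are shown and neither overrides the other.

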### 2.6. Procedures

#### 2.6.1. Buprenorphine/Naloxone Induction and Stabilisation

On the first day of admission to the inpatient unit, participants' pupil reflexes will be measured to provide a baseline for monitoring craving and medication response. Then, at the first sign of withdrawal, a three-day or five-day supervised BUP/NX-F induction will commence for individuals with morphine/heroin use disorder or pharmaceutical OUD, respectively. The longer induction period for the latter group reflects the relatively longer half-life of these products compared to heroin.

BUP/NX-F will be initiated at a dose of 2 to 4 mg will be used for those with a COWS score of <10. The participant will be closely observed during the first 4 hours to signs of precipitated withdrawal, together with regular pupil reflex monitoring and COWS assessments. The participant's dose will be increased by 2 to 4 mg to a maximum of 8 mg in the first 24 hours. On the second day of induction, the dose will be increased by 4 to 6 mg every 4 to 6 hours to a maximum of 24 mg per day.

With an achieved COWS score of <5, the participant will be transferred to an “early recovery unit” a step-down phase to achieve BUP/NX-F stabilisation. Each participant will be assigned to a personalised dosing schedule (i.e., daily, alternate-day [Alt-D] or thrice-weekly [TIW]) followed by further dose adjustment as required. Those who continue to report distressing opioid craving or do not tolerate their dosing schedule satisfactorily will be transferred to another (usually more frequent) schedule. The published correlation of patient characteristics and BUP/BUP/NX maintenance doses [51, 52] will serve as the theoretical basis for this regimen and the daily, or the total 24-hour dose, required to achieve a COWS scores <5 will be used as the reference for estimating non-daily doses.

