The Alt-D schedule will be a 3 × 48-hour dose and 1 × 24-hour dose. The TIW schedule will be a 2 × 48-hour dose and 1 × 72-hour dose (calculated as 3 × 24-hour dose at a maximum of 32 mg) [53, 54]. Clinical determination of the dosing schedule was informed by illicit injecting status (i.e., participants injected street heroin/morphine will receive daily doses and noninjected heroin and morphine users received alternate daily doses) while prescription opioid users (nonpolysubstance users) will receive TIW doses. Additionally, participants with severe psychiatric comorbidity, polysubstance use, or a body mass index (BMI) of ≥30 will be placed on the next higher frequency schedule (e.g., from TIW to ALT-D). Fine dose adjustments will be guided by self-report participant comfort, sleeping, craving, and pupil reflexes. Participants continuing to observe craving and or signs of withdrawal will be transferred to the next frequent dosing schedule towards the daily schedule as illustrated by Figure 1.

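### The planned dose–outcome correlation ignores dosing schedule, so a dose association can appear when dose has no effect, with a sign that depends on the dose scale

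*Protocol article*

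**What the plan says.** Section 2.2 of the protocol article makes the association of two buprenorphine parameters, elimination rate and dose, with opioid use and retention part of the first exploratory aim. Section 2.7.3 repeats it as an outcome: "There is correlation of participant demographics, clinical data, BUP EL.R, and BUP/NX-F maintenance dose with the primary and second outcome".

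Section 2.10 gives the method in three steps:
- "Bivariate correlation tests to explore correlations with study outcomes will be performed";
- factors that correlate significantly, or might affect the primary outcome, "will be studied for predictive power using a simple linear regression model";
- lastly, "analysing for the effect of confounders will be done using univariate analyses for factors generating higher correlation (>0.5").

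Section 2.6.1 says how schedule is set. "Clinical determination of the dosing schedule was informed by illicit injecting status": injectors of heroin or morphine dose daily, non-injecting users on alternate days (Alt-D), and prescription-opioid users without polysubstance use three times a week (TIW). Further, "participants with severe psychiatric comorbidity, polysubstance use, or a body mass index (BMI) of ≥30 will be placed on the next higher frequency schedule". Those with continuing craving or withdrawal "will be transferred to the next frequent dosing schedule towards the daily schedule".

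On the amounts, non-daily doses are worked out from the 24-hour dose that brings the COWS score below 5. The Alt-D week is three 48-hour doses and one 24-hour dose. The TIW week is two 48-hour doses and one 72-hour dose, the latter being three times the 24-hour dose with a 32 mg maximum. No multiplier is stated for the 48-hour dose. The article does not say whether the maintenance dose to be correlated is the 24-hour reference, the amount per administration or the average per day.

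**The concern.** Schedule is tied to both sides of the correlation.

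On the outcome side, several features that set schedule are ones the article connects with prognosis. The Introduction says mental health comorbidity may compromise response, and that depression and anxiety are often reported to predict discontinuation and heroin use. The Discussion counts the lack of stratification as a possible limitation and names type and pattern of opioid use, polysubstance use, anxiety and depression among the factors forgone.

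On the dose side, the same 24-hour requirement becomes a different number of milligrams under each schedule.

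A correlation that pools the schedules mixes any effect of dose with the difference between the kinds of patient placed on each schedule. Dose is one of only two drug parameters singled out, section 2.9 applies two-sided 5% tests to all analyses, and significant factors go forward as predictors. A significant result might only restate who was on which schedule.

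**Working it through.** The plan gives no figure for this analysis, so there is none to reproduce. The check has three parts.

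**1. What schedule does to the dose number.** Let D be the 24-hour dose. Assume the 48-hour dose is 2D (presumed, not stated) and the 72-hour dose is min(3D, 32), as section 2.6.1 states. Weekly totals are 7D (daily, 7 administrations), 3×2D + D = 7D (Alt-D, 4 administrations) and 2×2D + min(3D, 32) (TIW, 3 administrations).

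| D | Scale | Daily | Alt-D | TIW |
|---|---|---|---|---|
| 12 mg | per administration | 12 | 84/4 = 21.0 | (48+32)/3 = 26.7 |
| 12 mg | per day | 12 | 84/7 = 12 | 80/7 = 11.4 |
| 16 mg | per administration | 16 | 112/4 = 28 | (64+32)/3 = 32 |
| 16 mg | per day | 16 | 112/7 = 16 | 96/7 = 13.7 |

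From daily to TIW, dose per administration rises. Dose per day is flat, and then falls where the maximum binds (3D > 32, so D > 10.7 mg). If outcomes improve in the same direction, the first scale gives a positive correlation and the second a negative one.

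**2. False-positive rate of the planned test.** The true dose effect is zero and the outcome is the percentage of negative screens. None of the following is in the documents: 40/35/25% of participants on daily/Alt-D/TIW; mean negative screens 50/60/70% (a 10-point gap per step); outcome SD 30 points; 24-hour dose SD 4 mg. Section 2.8's figure of 92 gives n = 184 if it is per group and n = 92 if it is the total. The test is Pearson at two-sided 5%, with 3,000 simulated trials per setting; repeat runs agree within about three percentage points. At n = 184:

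| Mean 24-hour dose by schedule | Scale | Mean r | Significant |
|---|---|---|---|
| equal (12 mg) | 24-hour reference | 0 | 5–6% |
| equal (12 mg) | per administration | +0.17 | about 65% |
| equal (12 mg) | per day | −0.03 | 6% |
| 14/12/10 mg | 24-hour reference | negative | 23% |
| 14/12/10 mg | per administration | +0.12 | 38–39% |
| 14/12/10 mg | per day | −0.11 | 30–31% |
| 16/12/8 mg | 24-hour reference | negative | 58% |
| 16/12/8 mg | per administration | +0.05 | 9% |
| 16/12/8 mg | per day | −0.16 | 60–61% |

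Take four of these cells: equal per administration, 14/12/10 per administration, 14/12/10 per day and 16/12/8 per day.
- Gap halved to 55/60/65%, n = 184: about 22, 14, 12 and 21%.
- 10-point gap, n = 92: about 39, 22, 18 and 34%.
- Both changes together: none above about 13%.
- No gap between schedules: about 5% throughout.
- Schedule in the model: 4 to 6% in every setting.

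The size also moves with the assumed spread. With equal thirds on each schedule, an outcome SD of 20 points, a 10-point gap and 12 mg throughout, the per-administration rate is 68% at n = 92 and 92% at n = 184. It again returns to about 5% within schedule.

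**3. Would the confounder step catch it?** At n = 184 a correlation is significant from |r| = 1.973/√(1.973² + 182) = 0.145, well below the 0.5 threshold. Schedule itself would not reach 0.5 against the outcome. Scored −10/0/+10 points at 40/35/25%, its variance is 0.65×100 − 1.5² = 62.75, so r = √62.75/√(62.75 + 900) = 0.26. Even if the step were triggered, a univariate analysis does not adjust dose for schedule.

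**The case against.** The strongest reply has four parts.

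- **The aim is association, and exploratory.** A pooled correlation that reflects schedule is still a true marginal association. This stands as far as it goes: reported as pure description, the result would not be false. But the plan tests at 5% and then studies significant factors for predictive power, which invites more than description.
- **The 24-hour dose is a natural reading of maintenance dose.** On that scale, with equal doses across schedules, there is no artefact. This is correct. The article does not fix the scale, however. It also rests the regimen on a published relation between patient characteristics and dose, and adjusts dose on craving and sleep, so equality across schedules cannot be taken for granted.
- **The prognosis gap is assumed.** This stands in full. The Introduction supports comorbidity as prognostic, but the article does not say that injecting status or BMI is.
- **An article need not list covariates.** That is true of an omission. Here the article does fix a method, and every step of it is unadjusted.

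A reader might infer that the trial will probably report a spurious dose effect. The documents do not support that: several settings above stay near 5%, and no gap or schedule mix is given. A reader might also extend the point to the elimination rate. Nothing in the article shows schedule rescaling that parameter, so the extension is not made here.

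**Conclusion.** The point holds in conditional form. The method fixed in section 2.10 does not separate dose from dosing schedule, and under section 2.6.1 schedule is linked to patient features and changes the dose number. A dose–outcome association can therefore appear with no dose effect, and its sign depends on the scale used. With an outcome SD of 30 points and gaps of 10 or 5 points, the false-positive rate runs from about 5% to about 65%, and conditioning on schedule restores 4 to 6%. These rates rest on an assumed gap, schedule mix, spread and 48-hour multiplier. They were worked out for the primary outcome only; the same reasoning applies to retention but was not simulated.

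This concerns an exploratory analysis. The comparison between randomised groups is not affected, and nothing here bears on which dose or schedule is appropriate.

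**What to change.** In sections 2.7.3 and 2.10, and in the analysis plan:

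1. Define dose as mg per 24 hours for every participant. Say whether this is the 24-hour reference or the weekly amount divided by seven, since the two differ on TIW where the 32 mg maximum binds. State the 48-hour multiplier used in the calculation.
2. Replace the unadjusted dose correlation with a regression of the outcome on that dose, including dosing schedule and randomised arm, or report the association within schedule.
3. Add a sensitivity model with the factors that assign schedule: injecting status, opioid type, polysubstance use, psychiatric comorbidity and BMI.
4. Report the result as exploratory and observational. Dose is titrated to symptoms, and participants with continuing craving or withdrawal change schedule, so confounding remains within schedule. The 4 to 6% above reflects a simulation with confounding by schedule only.

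The cost is a change of wording, using information the protocol already relies on to assign schedule. The price is wider intervals for the dose association and some collinearity between schedule and its assignment factors, which is why those factors belong in a sensitivity model.
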